#### Sub-study 1: community cohort

Population, Intervention, Comparison and Outcome (PICO) framework (table 1).

**Table 1 T1:** Population, Intervention, Comparison and Outcome framework for sub-studies 1 and 2

	Sub-study 1	Sub-study 2
Population	People of any age with a recorded diagnosis of intellectual disability (ICD-10 code F7x), autism (ICD-10 code F84) or both, with at least 1 year of care under secondary mental healthcare services	People of any age with a recorded diagnosis of intellectual disability (ICD-10 code F7x), autism (ICD-10 code F84) or both, with at least 1 year of care under secondary mental healthcare services and an admission to a psychiatric inpatient ward for a period of at least 14 days
Intervention	Community C(E)TR	Community C(E)TR within 6 months prior to admission
Comparison	No community C(E)TR	Did not receive a community C(E)TR within 6 months prior to admission
Outcome		
Primary	Psychiatric hospital inpatient admission within 6 months of the community C(E)TR	Length of psychiatric hospital admission (days)
Secondary	Descriptive data and comparison of baseline demographics between intervention and comparison groups	Descriptive data and comparison of baseline demographics between intervention and comparison groups
	Descriptive data of 6 months pre-C(E)TR/post-C(E)TR (index date): neuropsychiatric symptoms, clinical variables and service use	Descriptive data and comparison of prehospital admission neuropsychiatric symptoms, HoNOS and service use Clinical and social functional improvement (change in HoNOS) while in hospital

C(E)TR, Care (Education) and Treatment Review; HoNOS, Health of the Nation Outcome Scales.

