### Study eligibility criteria

Individuals of any age with a diagnosis of intellectual disability (ICD-10 code F7x) or autism (ICD-10 code F84) will be identified using diagnostic information entered into structured fields or in the free text record using the NLP diagnosis application. Participants must have a recorded diagnosis of intellectual disability and/or autism. Eligible participants must have received an episode of care from a community mental health service provided by SLaM for at least one continuous year between 1 January 2015 and 31 December 2023 to ensure that sufficient data are held in the record. All eligible episodes of care will be included, including those individuals with more than one period of community care of at least 1 year during this timeframe.

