### Index date

The index date will be defined as the date of admission to a psychiatric hospital.

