### Inclusion and exclusion criteria

All eligible patients who were admitted to a psychiatric hospital for at least 14 days may be included in this study. We will exclude people who were not open to a SLaM community team for at least 6 months prior to their admission, as these people may have a high degree of missing data and may not have had an opportunity for a community C(E)TR before their admission or might represent new transfers from other NHS Trusts. We will also exclude ‘re-admissions’, defined as an admission occurring <6 months after the discharge date of a previous admission.

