#### Time-to-event analysis

Time-to-discharge (length of hospital admission) will be analysed using the Kaplan-Meier estimator.^19^ A Cox’s proportional hazards model will be used to estimate the HR for discharge,^20^ comparing those who received a C(E)TR to those who did not receive a C(E)TR for a follow-up period of 6 months after admission. This analysis will be adjusted for C(E)TR status prior to admission, age at admission, sex, ethnicity and relevant diagnosis at admission (intellectual disability with/without autism, or autism alone). Patients who die within 6 months of admission will be censored at the date of death, and patients who remain in hospital will be censored at the end of the 6 months.

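### Sub-study 2: the qualifying year of care is not tied to the admission date, so some patients can enter only through care received after the index date

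*Protocol article*

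**What the plan says.** Three places in the protocol article set care requirements for sub-study 2.

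- **Study eligibility criteria**, which covers both sub-studies, says participants "must have received an episode of care from a community mental health service provided by SLaM for at least one continuous year". The year is placed only in a calendar window, "between 1 January 2015 and 31 December 2023 to ensure that sufficient data are held in the record".
- **Table 1**, population for sub-study 2, describes people "with at least 1 year of care under secondary mental healthcare services and an admission to a psychiatric inpatient ward" of at least 14 days. This wording is not limited to community care, does not say the year is continuous, and gives no date to which the year relates.
- **Inclusion and exclusion criteria** for sub-study 2 starts from all eligible patients and adds: "We will exclude people who were not open to a SLaM community team for at least 6 months prior to their admission". This is the only care requirement tied to the admission.

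For sub-study 2, "The index date will be defined as the date of admission to a psychiatric hospital". Table 1 names length of admission in days as the primary outcome. Time-to-event analysis compares the groups on time to discharge "for a follow-up period of 6 months after admission", using Kaplan-Meier and a Cox model. The Cox model adjusts for age, sex, ethnicity and diagnosis, and not for duration of prior care.

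**The concern.** Eligibility for a cohort that starts at admission should be decidable on the day of admission. Here it is not, for one group: people with at least 6 but less than 12 months of community care before admission and no earlier qualifying year. They pass the 6-month rule but have not yet completed a year, so what happens after the index date decides whether they are in the analysis.

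Take a patient open to a community team for 8 months when admitted, in a setting where inpatient days count. A 4-month stay completes the year and brings the patient in. A 3-week stay followed by closure of the case leaves the patient out. Length of stay, the outcome, has then helped to choose who is analysed.

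Two things are at stake. The Kaplan-Meier description of length of stay can be shifted by this selection. The hazard ratio can be shifted too, if the C(E)TR and no-C(E)TR groups differ in how many such patients they contain or in what care follows discharge. A rule that can be read in more than one way may also be coded differently at the replication site, whose data cannot be pooled with the primary site's.

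**Working it through.** The protocol gives no sample size, event count or length-of-stay figure that bears on this, so there is no stated figure to reproduce. The check is a comparison of the wordings, date arithmetic, and an illustration on stated assumptions.

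**1. How the wordings relate.** A continuous community year (Study eligibility criteria) is also a year under secondary mental healthcare (Table 1), but not the reverse. The two are nested, with Table 1 the looser. Neither refers to the admission date.

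**2. Care still needed after admission.** With m months of prior care, the remainder is (12 − m) × 365.25/12 days.

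| Prior care (months) | Days still needed |
|---|---|
| 6 | 183 |
| 8 | 122 |
| 10 | 61 |
| 12 | 0 |

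The range of 0 to 183 days coincides with the 6-month follow-up for discharge.

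**3. How inclusion depends on stay, if inpatient days count.** Assumptions, none from the protocol:

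- prior care P is uniform over 183 to 365 days, with no earlier qualifying year;
- a share d of patients leaves all care at hospital discharge, and the rest have ample aftercare;
- stay L is 14 days plus an exponential variable, with overall median 60 days.

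A patient who leaves care at discharge is included only if P + L ≥ 365. For L up to 182 days this has probability L/182, so

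Pr(included | L) = 1 − d × (1 − L/182), and 1 for longer stays.

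Stays under 30 days average about 21.7 days under this distribution, and 21.7/182 = 0.119. With d = 0.5, inclusion is 1 − 0.5 × 0.881 = 0.56. A simulation of 2,000,000 patients gives the same:

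| d | Included, stay < 30 days | Included, stay ≥ 183 days | Median stay of those included (all: 60) |
|---|---|---|---|
| 10% | 91% | 100% | 62 days |
| 30% | 74% | 100% | 66 days |
| 50% | 56% | 100% | 72 days |
| 100% | 12% | 100% | 107 days |

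These figures describe only the 6-to-12-month group.

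**4. Dilution in the whole cohort.** Assume this group is 10% to 30% of the cohort, 20% to 60% leave care at discharge, and stay is log-normal (median 60 days, sigma 1, minimum 14 days). The whole-cohort median then moves from 60 to between about 60 and 64 days.

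**5. Effect on the hazard ratio when there is no true effect.** The assumptions are those of step 3, with median stay 30, 60 or 120 days, d = 10%, 30% or 50%, and unadjusted estimates over 183 days:

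| Share with 6-12 months of prior care (C(E)TR vs none) | Null HR for discharge |
|---|---|
| 20% vs 20% | 0.998 to 1.002 |
| 5% vs 15% | 1.001 to 1.021 |
| 10% vs 30% | 1.002 to 1.043 |
| Year required before admission | 0.998 to 1.002 |

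The first and last rows equal 1.00 within simulation error.

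**6. The strict community reading.** If admission closes the community episode, inpatient days do not count. The patient then needs another full community year ending by 31 December 2023. Inclusion depends on aftercare and remaining calendar time, and on the stay only indirectly. This reading was not simulated.

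**The case against.** The strongest reply is that Study eligibility criteria is the governing rule, that sub-study 2 takes it over by starting from all eligible patients, and that Table 1 is a short summary using the same phrase in both columns. That stands. A reader might infer that the two wordings contradict each other, but they are nested. The governing rule nevertheless has the same gap: its year may fall anywhere in nine calendar years, before or after admission.

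A reader might also infer that the two wordings select on length of stay in opposite directions, one favouring long stays and the other losing them. The document does not support this. One direction needs cases to be closed at discharge. The other needs admission to end the community episode and too little time to remain before the end of 2023. The protocol states none of these.

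Nor does the 6-month exclusion show an intention to admit people who finish the year later. Its stated reasons are missing data, lack of opportunity for a C(E)TR, and transfers from other Trusts. It would still do work if the year had to precede admission: someone with a qualifying year in 2016 who was re-referred weeks before a 2022 admission meets the year and fails the 6 months.

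Finally, the distortion is small on any plausible scenario examined, and the planned estimate is a hazard ratio and not a median. This stands too, and it limits the weight of the point. It does not remove it, because the rule as written uses information from after the index date. That is a property of a stated criterion and not a detail left to a fuller plan.

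**Conclusion.** The point holds in a limited form. As written, people with 6 to 12 months of community care before admission and no earlier qualifying year can enter sub-study 2 only through care received after admission. The dependence on length of stay is direct under the Table 1 wording, or if the community episode stays open during admission. It is indirect under a strict community reading.

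The size is unknown, because the protocol does not give the share of such patients or the pattern of aftercare. On the assumptions above, the null hazard ratio stays between about 1.00 and 1.04, and it departs from 1 only when the groups differ in prior care; a difference in aftercare could act in the same way. It would be wrong to infer that the planned hazard ratio is seriously biased. The Kaplan-Meier description can be shifted even with identical groups, by an amount that is diluted as the affected share falls.

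**What to change.** State in Study eligibility criteria, in Table 1 and in the sub-study 2 Inclusion and exclusion criteria that, for sub-study 2, the continuous community year must be completed on or before the date of admission. Keep the existing requirement of 6 months open to a community team before admission. Align the Table 1 population with the main text, so that both specify continuous community care. Inclusion through this criterion then no longer depends on the stay.

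The cost is a wording change, one date filter at each site, and the loss of people who complete the year only after admission.

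Dropping the year for sub-study 2 and keeping only the 6-month rule would also remove the dependence, but it is less attractive. It gives up a criterion that the protocol justifies by sufficiency of data. It also widens the manual record review, because C(E)TRs are searched for only in people who meet the eligibility criteria.

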### Index date

The index date will be defined as the date on which a community C(E)TR was held.

### Exposure

Exposure will be defined as the community C(E)TR.

### Descriptive measures

Baseline measures extracted at the index date will include age, sex, ethnicity, deprivation score (Index of Multiple Deprivation),^11^ and other socio-demographic, mental and physical health indicators (online supplemental table 1).

### Outcome

The primary outcome will be psychiatric hospital admission (treated as a binary variable) at any time within 6 months after the index date (online supplemental table 2).

### Matching a control group

We will match between one and five controls, who will not have a community C(E)TR, per patient who has a C(E)TR. Eligibility will be a diagnosis of intellectual disability or autism and having received a continuous period of community care within SLaM services for at least a year between 1 January 2015 and 31 December 2023. Matching will be based on age (±3 years), sex (male/female) and diagnosis (intellectual disability with/without autism, or autism without intellectual disability). Controls should be under an active episode of community care and not be an inpatient on the index date of their matched case. They must also have been under SLaM services for a similar total duration of their matched case (±2 years). Matching with replacement will be applied to ensure every case has an appropriate match according to these criteria. A pseudo-index date for each control will be assigned and will be the same as the index date of their matched case.

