## Introduction

 Reducing unnecessary psychiatric hospital admissions and length of hospital stay for people with intellectual disability and autistic people has been a focus of English national health policy since the scandal of abuse and neglect of patients at Winterbourne View Hospital in 2011.^1^ The Transforming Care programme was established to improve community health and social care for people with intellectual disability and autistic people and to reduce what had generally been considered to be an over-reliance on inpatient psychiatric services.^2^ A key element of Transforming Care has been the introduction of Care (Education) and Treatment Reviews (C(E)TRs), person-centred review meetings that aim to ensure the right support is provided.^3^ A community C(E)TR should be convened when a person with intellectual disability or an autistic person living in the community is considered at high risk of admission to a psychiatric hospital, either because of mental ill-health or because of an escalation in behaviours that challenge. C(E)TRs are chaired by a health commissioner and include an independent clinical expert and an expert-by-experience, often a family carer of a person with intellectual disability or an autistic person. This panel gathers information from the individual, their families and carers, and professionals, and produces a report and action plan following the C(E)TR with recommendations (eg, input from specialist professionals or health teams, provision of additional care, use of respite services) that can enable the person to remain living safely in the community. Where admission to hospital is considered necessary, the C(E)TR panel will define the purpose of the admission and encourage early discharge planning in order to minimise the length of the hospital stay. Inpatient C(E)TRs are convened at various points of a hospital admission; the current project investigates only C(E)TRs that are held in the community.

Little formal research has been carried out on community C(E)TRs, such as who receives them and when, and how C(E)TRs may influence health service use, including admission to hospital. By understanding the demographic and clinical profile of patients who do, and do not, have a community C(E)TR, it may be possible to develop targeted interventions to improve access to community C(E)TRs and ensure the potential benefits are available to everyone.

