## Methods and analysis

### Study setting

Data will be obtained from the South London and Maudsley (SLaM) NHS Foundation Trust. SLaM is one of the largest providers of secondary mental healthcare in Europe, with a diverse catchment area of approximately 1.3 million people who live in the south London boroughs of Lambeth, Southwark, Lewisham and Croydon. Mental health services provided by SLaM include specialist teams for children and adolescents with mental illness and/or neurodevelopmental conditions, community teams for adults, including specialist teams for those with intellectual disability, and mainstream and specialist inpatient wards across different sites. The Trust has implemented a full EHR since 2006, and the SLaM NIHR Maudsley Biomedical Research Centre Case Register contains the clinical records of >5 00 000 patients.^4 5^ Unless otherwise stated, data will be extracted up to an end date of 31 December 2024. The protocol for this study was finalised in July 2025. Data extraction is anticipated to be complete by September 2025 and data analysis by December 2025.

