### Identifying cases and controls

Using the review of clinical records of eligible patients previously described, we will measure whether each patient had a community C(E)TR within 6 months prior to their psychiatric hospital admission. We will form two groups: those who had a pre-admission community C(E)TR, and those who did not.

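### Eligibility and matching do not require the intellectual disability or autism diagnosis to be recorded by the index or admission date, so people first diagnosed later can enter the comparison groups

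*Protocol article*

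**What the plan says.** Under Study eligibility criteria the article requires a diagnosis without dating it: "Participants must have a recorded diagnosis of intellectual disability and/or autism". On its source, the same section says that eligible individuals "will be identified using diagnostic information entered into structured fields or in the free text record using the NLP diagnosis application". Table 1 repeats the requirement for both sub-studies, again undated. Under Study setting, "data will be extracted up to an end date of 31 December 2024" unless otherwise stated.

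For sub-study 1, the section on matching a control group sets the rule "Eligibility will be a diagnosis of intellectual disability or autism and having received a continuous period of community care within SLaM services" and then matches on age, sex and diagnostic category. Two other conditions in that section are dated: "Controls should be under an active episode of community care and not be an inpatient on the index date of their matched case".

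For sub-study 2, "All eligible patients who were admitted to a psychiatric hospital for at least 14 days may be included in this study". The two groups are "those who had a pre-admission community C(E)TR, and those who did not".

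The Introduction describes the people for whom the review is meant, the risk in question being psychiatric admission: "A community C(E)TR should be convened when a person with intellectual disability or an autistic person living in the community is considered at high risk".

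**The concern.** A community C(E)TR is meant for someone understood to have intellectual disability or to be autistic. Whoever had one was in practice recognised as such by then. A comparator need not have been, because a diagnosis entered at any point up to the end of extraction meets the rule as worded. The gap therefore falls mainly on the comparison side.

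Two things are at stake. The first is comparability. A control not yet recognised at the pseudo-index date was unlikely to be considered for a C(E)TR and may have been managed as a general mental health patient, yet would be matched and weighted as if recognised. The second is selection on the future. A psychiatric admission is an occasion for assessment, and a long one more so. If the diagnosis comes out of that admission, the outcome itself brings the person into the comparison group. This matters most in sub-study 1, which aims at a causal effect on admission, and for length of stay in sub-study 2.

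**Working it through.** The article gives no sample size, event rate or share of late diagnoses, so there is no figure to reproduce. The check compares every rule that fixes the timing of the diagnosis or of a related condition.

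**1. Eligibility.** Study eligibility criteria and Table 1 require a recorded diagnosis. Neither gives a date relative to index or admission.

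**2. Control matching (sub-study 1).** Active community care and non-inpatient status are fixed at the matched index date. Diagnosis, both as an entry condition and as a matching variable, is not.

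**3. Range of dates.** Qualifying care starts on 1 January 2015 and extraction ends on 31 December 2024. Someone in community care at a 2016 pseudo-index date and first diagnosed in 2022 can meet every stated control condition.

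**4. Sub-study 2 inclusion.** It takes the same eligible patients, with a stay of at least 14 days and at least 6 months with a community team before admission. One stated reason for the 6-month rule is that people with less time in the service may have had no chance of a C(E)TR. The same reasoning applies to a person not yet recognised as having intellectual disability or autism, but no rule covers that case.

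**5. Covariates.** The propensity model lists the relevant diagnosis among pre-index characteristics. The Cox model uses the relevant diagnosis at admission. Each has two categories and none for a person not yet diagnosed. These passages suggest that the diagnosis is meant to be known at baseline, but they exclude nobody.

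**6. Direction, sub-study 1.** Let s be the (weighted) share of controls first diagnosed after the pseudo-index date, pL their post-index admission risk and p0 that of the other controls.

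- Shift in control post-index risk = s × (pL − p0).
- Illustration on assumed values, none from the article: p0 = 10%, pL = 20% to 30%, s = 5% to 20%.
- Low end: 0.05 × (0.20 − 0.10) = 0.005, or 0.5 percentage points.
- High end: 0.20 × (0.30 − 0.10) = 0.04, or 4 percentage points.
- If pL > p0, control risk rises and the comparison favours the C(E)TR. If pL < p0, the sign reverses. If s = 0, there is no shift.

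This applies directly to the fallback logistic regression on post-index status. In the difference-in-differences model the pre-index risks (qL and q0, defined likewise) count too, and the control change shifts by s × [(pL − p0) − (qL − q0)]. A stable difference in risk would cancel. A difference that arises because the post-index admission produced the diagnosis would not.

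**7. Direction, sub-study 2.** A person first diagnosed during the index admission falls in the unexposed group unless a C(E)TR preceded it, which is unlikely. More days in hospital give more time to be diagnosed and so become eligible. This tends to over-represent long stays among the unexposed, lower their discharge hazard and move the hazard ratio in favour of the C(E)TR. A diagnosis first made after discharge carries no such direct link with length of stay, but it still weakens comparability.

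**The case against.** The best reply is that silence is not a rule. The article does not say that a diagnosis at any time suffices. Its Natural language processing section refers to a surveillance period, its Descriptive measures section takes baseline measures at the index date, and both models date the diagnosis as a covariate. An article may leave extraction logic to a fuller document or to supplementary tables that are not shown. If the matching category were read at the index date, the sub-study 1 gap would close. The minimum periods of community care also give time for a diagnosis to be recorded.

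This supports the likely intent, and it shows that the number affected may be small. It does not settle the point. The article does set out its eligibility and matching rules, and it dates some conditions but not this one. A data extract built to those rules would admit later-diagnosed people.

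Three stronger readings are tempting but unsupported:

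- **That such controls violate overlap.** The stated estimand is the average effect on the treated. It needs comparable controls for treated patients, that is, a treatment probability below 1 at their covariate values. It does not need every control to have had a chance of treatment. The problem is comparability and misclassified baseline status.
- **That these people could not have received a C(E)TR.** The Introduction does not make a coded diagnosis in this Trust's record a condition. A diagnosis known elsewhere may be entered late.
- **That the bias can be put in days of stay.** This would need an assumed share and assumed mean stays, and a difference in means is not on the scale of an adjusted hazard ratio censored at 6 months.

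**Conclusion.** The point holds as a gap in the stated rules: in both sub-studies, people first diagnosed after index or admission can serve as comparators. It does not follow that many will. The share is unknown, and the percentage points above illustrate a formula on assumed inputs; they are not an estimate.

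In sub-study 2 the likely direction favours the C(E)TR, on the assumption that some diagnoses are made during the index stay and are likelier the longer it lasts. In sub-study 1 the direction is open. The fault is mainly one-sided, on the assumption that C(E)TR recipients were already recognised at the time. It should be corrected because selection may depend on the outcome and the remedy is simple.

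**What to change.** In Study eligibility criteria, Matching a control group, and the sub-study 2 Inclusion and exclusion criteria, add one condition for both groups: the first recorded diagnosis of intellectual disability or autism, whether a structured entry or a dated free-text mention, must fall on or before the index or pseudo-index date (sub-study 1) or the admission date (sub-study 2). Assign the matching and adjustment categories from records up to that date. Report by group how many people the condition removes, which also shows how large the issue was. Keep the any-time definition as a sensitivity analysis.

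The cost is one date condition, provided that the dates of entries and documents are kept in the extract. The pool becomes somewhat smaller, which the allowance of one to five controls per case and matching with replacement soften in sub-study 1 but not in sub-study 2. Some people who were recognised in practice but recorded late will be lost, possibly in either group. The sensitivity analysis is there to show whether that matters.
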